### RE-AIM: Maintenance

Maintenance is assessed at the staff level and setting level [26,27]. At the staff level, maintenance will be assessed by using the health care professionals’ self-report of continued use using the Provider Report of Sustainment Scale (PRESS) at 6 and 12 months post implementation [44]. The PRESS measure is a brief, reliable, and valid 3-item measure that is both pragmatic and usable across different evidence-based practices, provider types, and settings. The PRESS captures health care professionals’ reports of continued use of an intervention in daily practice. In addition, health care professional level maintenance will also be assessed by using the health care professionals’ self-efficacy and performance using the SEPSS-36 at 12 months post implementation [40].

At the setting level, maintenance will be assessed via the Clinical Sustainability Assessment Tool (CSAT) [45]. The CSAT is a brief and reliable instrument consisting of 35 items within 7 domains to assess an institution’s capacity for maintaining a clinical practice. These domains are (1) engaged staff and leadership, (2) engaged stakeholders, (3) organizational readiness, (4) workflow integration, (5) implementation and training, (6) monitoring and evaluation, and (7) outcomes and effectiveness. CSAT development and testing demonstrated excellent internal consistency and several trends toward discriminant validity [45].

In addition to the questionnaires, the CFIR-informed interviews with burn physicians, nurse practitioners, aftercare nurses, and burn center managers will provide working hypotheses to explain the degree of individual (health care professional) and setting-level maintenance.

### Participant Timeline

The participant timelines illustrated in Table 2 (for survivors of burn injuries) and Table 3 (for health care professionals) outline the different assessment time points of the study.

**Table 2. T2:** Timeline for participating survivors of burn injuries: enrollment, interventions, and assessments.

	Study period – survivors of burn injuries				
	Enrollment	Allocation	Postallocation		Closeout
	Before discharge	At discharge	T1 (2 weeks postdischarge)	T2 (6 months postdischarge)	T3 (12 months postdischarge)
Enrollment					
Eligibility screen	✓				
Informed consent	✓				
Allocation		✓			
Interventions					
Control (usual care)^a^			✓	✓	✓
BreeZe aftercare^a^			✓	✓	✓
Assessments					
Demographics		✓			
Self-management skills (PiH^b^) [34]			✓	✓	✓
Self-regulation (SeRA^c^) [35]			✓	✓	✓
Participation (MeEAP^d^) [36]			✓	✓	
Daily activities (EQ-5D-5L) [37]			✓	✓	✓
Self-care (EQ-5D-5L) [37]			✓	✓	✓
Dependency			✓	✓	✓
Return to work or school (ICHOM^e^) [38]				✓	✓
Patient centeredness (CAHPS^f^) [39,53]				✓	
Quality of life (EQ-5D-5L) [37]			✓	✓	✓

a Duration of usual or BreeZe aftercare depends on the personal trajectory of the survivor of burn injuries.

b PiH: Partners in Health scale.

c SeRA: Self-Regulation Assessment.

d MeEAP: Measure of Experiential Aspects of Participation.

e ICHOM: Adjusted International Consortium for Health Outcomes Measurement.

f CAHPS: Consumer Assessment of Health Plan Survey.

**Table 3. T3:** Timeline for participating health care professionals: enrollment, interventions, and assessments.

	Study period – health care professionals				
	Enrollment	Allocation	Postallocation		Closeout
	Preimplementation phase	Implementation phase	T1 (3 months postimplementation phase)	T2 (6 months post implementation phase)	T3 (12 months postimplementation phase)
Enrollment					
Eligibility screen	✓				
Informed consent	✓				
Allocation		✓			
Interventions					
Training		✓			
Assessments					
Demographics	✓				
Self-management support skills (SEPSS-36^a^) [40]	✓		✓	✓	✓
Need-supportive counseling (COUNSEL-CCE^b^ and NCIT^c^) [41,42]	✓		✓		✓
Maintenance (PRESS^d^) [44]				✓	✓
Maintenance (CSAT^e^ ) [45]			✓		✓
CFIR^f^-informed interviews				✓	

a SEPSS-36: Self-Efficacy and Performance in Self-Management Support Questionnaire.

b COUNSEL-CCE: Coding and Observing Need-Supportive Counselling in Chronic Care Encounters.

c NCIT: Nurse-Child Interaction Taxonomy.

d PRESS: Provider Report of Sustainment Scale.

e CSAT: Clinical Sustainability Assessment Tool.

f CFIR: Consolidated Framework for Implementation Research.

### Sample Size

To estimate sample size, we used a power calculation based on our primary outcome, which is self-management skills measured by the PiH questionnaire. As no minimum clinically important difference is established in the literature, 2 burn care nurse practitioners examined the PiH and considered an improvement of 8 points as clinically relevant. Based on this face-validity score and a previous dataset with PiH data from survivors of burn injuries collected with the Burn Centers Outcomes Registry the Netherlands (BORN), a mean difference of 8 points between the control and intervention group is feasible. As there is no validated stepped-wedge–specific sample size calculator for this outcome, we used a pragmatic approximation based on this predefined clinically relevant difference we established. In addition, as there is no data available on potential ICCs and we have a small number of burn centers, we will take center difference later on into account by adding 2 dummy variables (with center 1 being the reference center) in our analyses [55]. For the sample size calculation, we used the online sample size calculator of the University of British Columbia [56]. We aim to obtain 80% power with a 2-sided significance level of 0.05. Due to the stepped-wedge design of our study, our allocation rate for the control group:intervention group will be 0.625:1. With an adjustment of 20% for dropouts, missing data, and fixed time effects taken into account, we calculated that 57 participants in the control group and 89 participants in the intervention group will be sufficient. This amount (n=146) is deemed sufficient for (multilevel) regression analyses using the MIwiN statistical program, version 3.10 [57].

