## Results

This research is part of a larger project, which was funded in January 2022. Participant recruitment ended on June 30, 2025. In total, 42 participants are included in the control group, and 53 participants are included in the intervention group. Follow-up data collection is currently ongoing and will end in July 2026. Data analysis will start in August 2026, and the results are expected to be published in May 2027.

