A last methodological consideration in designing this study is our aim to strike a careful balance between internal and external validity, ensuring that the study is both generalizable to different burn care settings and sufficiently rigorous and robust to provide reliable answers to our research questions. While a parallel cluster randomized design is often considered the gold standard for minimizing bias and ensuring strong internal validity, we opted for a nonrandomized stepped-wedge design [24,76,77]. A parallel cluster randomized design, in which all clusters are randomly assigned to either the intervention or control condition, is often challenging in real-world settings, as it requires immediate and simultaneous implementation across all centers. Implementation success strongly influences the outcomes of an intervention, and whether you achieve implementation success is strongly dependent on organizational readiness [59]. Also, a parallel cluster randomized design is potentially less acceptable for stakeholders, as at least 1 cluster acts as the control group, meaning they are not exposed to the potential benefits of the intervention [24,78]. In contrast, a nonrandomized stepped-wedge design allows for a staggered implementation, where all centers eventually receive the intervention but at different time points and is logistically feasible [24]. Hence, to increase stakeholder acceptability and organizational readiness, we made the choice not to randomize. However, a nonrandomized stepped-wedge design carries a greater risk of bias, particularly due to lack of randomization, time-related confounders, and potential differences between early and late adopters [79,80]. To control for these, we took fixed-time effects into account in our sample size calculation [81].

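### Recruitment closed at 95 patients against 146 planned for 80% power, with no restated figure, and a 20% allowance cannot also cover fixed time effects if calendar time is in the model

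*Protocol article*

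**What the plan says.** The Sample Size section sets the target: "We aim to obtain 80% power with a 2-sided significance level of 0.05". It judges that "a mean difference of 8 points between the control and intervention group is feasible", and adds that "our allocation rate for the control group:intervention group will be 0.625:1". The calculation comes from a generic online calculator and is described as a pragmatic approximation. One inflation figure appears: "With an adjustment of 20% for dropouts, missing data, and fixed time effects taken into account". The result is 57 control and 89 intervention patients, and "This amount (n=146) is deemed sufficient for (multilevel) regression analyses". A registry dataset is named as a source, but no SD is given.

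The Results section reports that recruitment has ended and that "42 participants are included in the control group, and 53 participants are included in the intervention group". It does not comment on the target.

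Methodological Considerations lists lack of randomization, time-related confounding and differences between early and late adopters as risks of the design, then says: "To control for these, we took fixed-time effects into account in our sample size calculation".

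The analysis section for the coprimary effectiveness outcome adds two center dummies. It leaves open how time will be modeled: continuously since discharge, or as categories. Season and time since the intervention started are listed among candidate covariates.

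**The concern.** There are two problems, and they add up.

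- **Shortfall.** The article prints a target and an achieved number that is 65% of it (95/146), and draws no consequence. The only power figure a reader finds is 80%.
- **Time effects.** A single 20% is said to absorb dropout, missing data and fixed time effects. In a three-center stepped-wedge design, treatment status and calendar time are strongly related, and adjusting for calendar time costs far more precision than 20%. The Discussion then presents the sample size as the control for time-related bias. A sample size affects precision; it cannot remove confounding.

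At stake is how precise the PiH comparison is understood to be, and whether readers believe that secular change has been dealt with.

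**Working it through.** **Inputs.** Difference 8 points, two-sided 0.05, 80% power, ratio 0.625:1, 20% allowance, 57 + 89 planned (Sample Size); 42 + 53 enrolled, recruitment to June 30, 2025 (Results); all centers start April 2024 and go live in June, September and November 2024 (Trial Design). The SD is not stated and is back-solved.

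**1. Reproducing 57 + 89.** n(intervention) = (1 + 1/0.625) × (1.960 + 0.842)² × SD² / 8², and n(control) = 0.625 × n(intervention).

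- SD 14.9: 44.2 and 70.8, rounded up to 45 and 71. Divided by 0.8: 56.25 and 88.75, so 57 and 89.
- SD 15.2: 46.0 and 73.7, rounded up to 47 and 74. Times 1.2: 56.4 and 88.8, so 57 and 89.

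Either route returns the stated numbers with the 20% fully used. The analysable number is 45 + 71 = 116 or 47 + 74 = 121.

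**2. Power at 42 + 53 on the same basis.** SE = SD × √(1/n₁ + 1/n₂); power = Φ(8/SE − 1.96).

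- No loss: SE 3.08–3.14, power 74–72%.
- 20% loss (34 + 42): SE 3.44–3.51, power 64–63%. The difference detectable with 80% power is 2.802 × SE = 9.6–9.8 points.

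**3. What 20% can cover.** If all of it went to time effects and none to loss, it would allow a variance inflation of 1.2 (multiplying by 1.2) or 1/0.8 = 1.25.

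**4. What adjustment costs.** Inflation = 1/(1 − R²), from regressing treatment status on the adjustment terms over 3 centers × 15 months, with 2, 5 and 7 control months. Assumptions: equal centers and steady accrual.

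- Total sum of squares: 14 × 31/45 = 9.644.
- Center only: residual 2×13/15 + 5×10/15 + 7×8/15 = 8.800. Inflation 9.644/8.800 = 1.10.
- Center + linear month: the within-center cross-products are 13 + 25 + 28 = 66 and the month sum of squares is 3 × 280 = 840, so the residual is 8.800 − 66²/840 = 3.614. Inflation 2.67.
- Center + month categories: the within-month sum of squares is 5 × 2/3 = 3.333 and the center part is 9.644 − 8.800 = 0.844, so the residual is 2.489. Inflation 3.87.

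Weighting accrual to 57:89 gives 2.99 (linear) and 4.24 (categories). Weighting it to 42:53 gives 3.18 and 4.44. Counting the go-live month as control (3, 6 and 8 months) moves the linear figure at 42:53 to about 3.3. The ranges are therefore about 2.7–3.3 and 3.9–4.4. Unequal center sizes widen them to 2.4–4.6 overall.

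**5. Power with adjustment.** Multiply the variance in step 2 by the inflation. SD is 14.9–15.2, with no baseline adjustment and no gain from repeated measures.

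| Model | Inflation | Analysed | Power |
|---|---|---|---|
| Center + time since discharge | 1.1 | 42 + 53 | 68–70% |
| Center + time since discharge | 1.1 | 34 + 42 | 59–60% |
| Center + linear calendar time | 2.7–3.3 | 34 + 42 | 24–29% |
| Center + calendar month categories | 3.9–4.4 | 34 + 42 | 19–22% |

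At the achieved 42:53 mix the linear inflation is at the upper end of its range, so 24–26% is the more relevant part of that row.

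**The case against.** - **Target, not claim.** The 80% is a planning aim, and the enrolled numbers are disclosed. A reader might infer that the article claims 80% power for the 95 enrolled; it does not. What stands is that the two figures are left unreconciled.
- **Ambiguous sentence.** The 20% could be for loss only, with time effects handled elsewhere. Because the SD is not given, a separate step cannot be strictly excluded. It would need an SD of about 7.6–9.2 (15.06/√3.9 to 15.06/√2.7), and no such step is described. One allowance for all three items remains the more natural reading.
- **Model not fixed.** A reader might infer that time effects always require about a threefold inflation. The documents do not support that: with center and time since discharge the inflation is about 1.1. But calendar confounding is then uncontrolled, although the analysis section motivates its time term by the different calendar periods of the two groups.
- **Repeated measures and baseline.** A reader might infer that power is below 80% under any analysis. That is not established. Illustration, assuming equal correlations of 0.5–0.7, T1 as covariate and the mean of T2 and T3 as outcome: the residual variance factor is (1 + r)/2 − r² = 0.50 to 0.36. Power at 34 + 42 is then about 87–96% at inflation 1.1 and 46–61% at inflation 3.0. The correlations are not in the documents, the primary model does not commit to T1 adjustment, and BreeZe starts before T1 for patients admitted for more than 24 hours, so T1 is an imperfect baseline.
- **Misreading.** Nothing in the article says that a non-significant result will be taken as no effect. A rule for reading such a result would be a preference, not a correction.

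**Conclusion.** The point holds in this form. Enrollment of 95 is below both the target of 146 and the 116–121 analysable patients implied by the plan's own calculation, and no revised figure is given. Under that simple calculation power is about 72–74% with no loss and 63–64% with 20% loss. This rests on a back-solved SD near 15, although the drop itself comes from calibrating to the plan's own 80%.

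The statement on fixed time effects is not supportable as written. The allowance covers at most 1.2–1.25, against about 2.7–3.3 or 3.9–4.4 if center and calendar time are both in the model. The resulting powers of roughly 24–29% and 19–22% are conditional on that model, equal centers, steady accrual and 20% loss. Baseline adjustment or repeated measures would raise them. The claim that the sample size controls time-related bias is wrong under any model.

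Confidence is high for the shortfall and for the limits of the 20%, and moderate for the adjusted power figures.

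**What to change.** 1. In Sample Size or Results, restate the power or the detectable difference for 42 + 53 under the intended analysis model and expected loss. Give the assumed SD and show the result as a range across the candidate time models, with and without baseline adjustment.
2. Remove fixed time effects from what the 20% is said to cover.
3. In Methodological Considerations, replace the statement that time-related bias was controlled through the sample size with adjustment for calendar time in the model, and say so in the analysis section.

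The cost is less favorable stated figures. No further patients are needed, and the text can be changed before analysis starts in August 2026.

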### Recruitment

As of July 15, 2022, all survivors of burn injuries receiving burn care in one of the 3 centers are asked by a nurse practitioner or aftercare nurse to complete the routinely collected value-based health care burns core set for adult survivors of burn injuries as part of the Dutch Burn Repository R3 and the BORN [58]. In addition to the routinely collected core set data, survivors of burn injuries who participate during the pre- and postimplementation phases of this study will be asked to complete additional questionnaires. A nurse practitioner or aftercare nurse will introduce the study to eligible patients and provide a patient information letter. After an appropriate consideration time (2 d), a member of the center’s research team will answer any questions about the study and take informed consent. By involving the nurse practitioners and aftercare nurses, all eligible survivors of burn injuries will be reached.

### Assignment of Interventions

#### Sequence Generation

We believe that a burn center’s enthusiasm to participate in the intervention serves as a preliminary indicator of its organizational readiness. Organizational readiness is a crucial determinant that influences the implementation success or failure [59]. Hence, we decided to determine the order of commencement based on our interpretation of the burn centers’ organizational readiness.

Patients will be recruited in consecutive order in the preimplementation phase as well as in the postimplementation phase. In principle, all health care professionals involved in burns aftercare will be recruited.

#### Blinding, Concealment Mechanism, and Implementation

Blinding is not feasible due to the nature of the intervention. As blinding is not feasible, no procedures for unblinding are necessary. Furthermore, due to the lack of blinding and randomization, no concealment mechanism is necessary. The sequence allocation of the centers has been chosen in deliberation with the BreeZe project team. In each center, 2 or 3 specialized researchers are responsible for enrollment and data collection.

### Data Collection and Management

#### Data Collection Methods

##### Survivors of Burn Injuries

Assessment time points are at discharge, 2 weeks after discharge, and 6 and 12 months after discharge, as pictured in Table 2. Questionnaires at 2 weeks after discharge and 12 months are part of the routinely collected value-based health care burns core set, from the BORN [58]. Participants receive the questionnaires by email. In cases where patients do not have an email address or access to a computer, the questionnaire can be completed by telephone interview or on paper. Using the Dutch Burn Repository R3, the characteristics sex, age, and total burned body surface area will be collected from all eligible survivors of burn injuries during the study period.

##### Health Care Professionals

Assessment time points with health care professionals are preimplementation, and at 3, 6, and 12 months post implementation, as pictured in Table 3. They will receive the questionnaires via email or on paper, distributed by the responsible researcher.

Consultations that are eligible for video observations will be discussed and selected by the research team and health care professionals. Consultations will be eligible if they qualify as an aftercare consultation. Survivors of burn injuries will be informed and asked by a member of the research team 1 to 5 days before their appointment if they agree that their encounter is filmed. Before the start of the consultation, the researcher sets up the video camera and starts the recording. Then, the researcher leaves the room, and the health care professional and the survivor of burn injuries will start the consultation. Both the health care professional and survivor of burn injuries will be visible in the recording. At the end of the consultation and when the health care professional and survivor of burn injuries have left the room, the researcher will stop the recording and transfer the recording directly from the camera to the specialized research file. After the transfer, the recording will be directly deleted from the video camera.

The interviews will be carried out by the main researcher. Beforehand, a CFIR-informed topic guide will be developed. The interviews will be recorded with a tape recorder and will last approximately 45 minutes.

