##### Health Care Professional Level Outcomes – Secondary Outcome Measures

Self-management support skills: The self-management support skills of the participating health care professionals will be assessed using the Self-Efficacy and Performance in Self-management Support (SEPSS) instrument [40]. The aim of the instrument is to assess self-efficacy and performance in self-management support. The six subscales of the SEPSS are based on the 5 A’s model, (1) assess, (2) advise, (3) agree, (4) assist, (5) arrange, and (6) overall competencies. This questionnaire shows good internal consistency (Cronbach α=0.96) as well as a good test-retest ICC (ICC=0.95).

Need-supportive counseling: The self-management support skills of the participating health care professionals will be objectively evaluated in the preimplementation and postimplementation phases, via video observations using the Coding and Observing Need-Supportive Counseling in Chronic Care Encounters (COUNSEL-CCE) [41]. The survivors of burn injuries and health care professionals who will be filmed will be asked to give consent. Each health care professional will be filmed at least once during the preimplementation and postimplementation phases. The aim of the instrument is to observe need-supportive and need-thwarting counseling in chronic care encounters. The COUNSEL-CCE consists of 44 items divided into nine scales of behavioral approaches, namely (1) participative, (2) attuning, (3) guiding, (4) clarifying, (5) demanding, (6) domineering, (7) abandoning, (8) awaiting, and (9) relatedness supportive reciprocity. The procedure for the observation is the observation of the interaction between the professional and the patient during a 5-minute interval, coding of the observed interval, and observing the same interval for a second time to code any aspects missed. Before scoring the video recordings, the researchers will be trained in the use of the manual, which is provided by the developers of the instrument.

In addition to the COUNSEL-CCE, the video recordings will also be evaluated using the Nurse-Child Interaction Taxonomy (NCIT) [42]. Although this taxonomy was originally developed to improve nurse-child communication, it can also be used to systematically document the interaction between nurses and adult patients. The NCIT consists of 16 elements divided into three main patterns, (1) being considerate, (2) attuning oneself, and (3) procedural intervention.

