#### Health Care Professionals

Health care professionals will be reminded by the responsible researchers to complete questionnaires, to select consultations for the video observations, and to set a date for the interviews.

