###### Health Care Professionals Level Outcomes – Secondary Outcome Measures

To evaluate the effect of the training on self-management support skills, we will use the data from the SEPSS-36 in a 2-level regression model with measurement occasions within a health care professional.

For the video observations, the video recordings will be broken down into 5-minute intervals. Each interval will be coded independently by 2 researchers according to the NCIT and COUNCEL-CCE coding manuals. Results will be presented with descriptive statistics. Differences in observations through time will be tested with (multilevel) regression analyses for repeated measures.

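### The rated professionals help choose which consultations are filmed, so the pre-to-post change in the video outcome can partly reflect the choice of visits if that choice differs between phases

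*Protocol article*

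**What the plan says.** The article gives one selection rule for filmed visits (Data Collection Methods, Health Care Professionals): "Consultations that are eligible for video observations will be discussed and selected by the research team and health care professionals". The only eligibility condition follows: "Consultations will be eligible if they qualify as an aftercare consultation". Under the retention plans, professionals are also reminded "to select consultations for the video observations", so their part in the choice is active. Patients are "asked by a member of the research team 1 to 5 days before their appointment if they agree that their encounter is filmed", so a visit is picked before it takes place and patient agreement is a further filter.

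The Outcomes section sets the minimum number of recordings: "Each health care professional will be filmed at least once during the preimplementation and postimplementation phases". It describes the purpose in these terms: "The self-management support skills of the participating health care professionals will be objectively evaluated in the preimplementation and postimplementation phases". Table 3 places the video ratings before implementation and at 3 and 12 months after it.

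On analysis, the Statistical Methods section says "Each interval will be coded independently by 2 researchers according to the NCIT and COUNCEL-CCE coding manuals" and "Differences in observations through time will be tested with (multilevel) regression analyses for repeated measures". It names no adjustment for the type or stage of the filmed visit. Blinding is stated not to be feasible. Patients, by contrast, are recruited consecutively in both phases (Sequence Generation).

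**The concern.** The people whose skill is rated take part in deciding which of their visits is rated, and both they and the research team know the phase. With as little as one recording per professional per phase, a single choice can determine that professional's score. Aftercare visits differ in content and in how cooperative the patient is, and a consultation score is likely to vary with both.

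The reported result is a change over time within professionals. If the visits filmed after training are picked more favorably than those filmed before it, or are of another kind, the change mixes skill with sampling. Two independent, trained coders reduce rating error but cannot correct which visits were put in front of them. At stake is whether a pre-to-post gain can be presented as objective evidence that training changed counseling behavior.

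**Working it through.** The article gives no sample size, variance or effect size for the video outcome, so there is no figure to reproduce. The size of the mechanism can only be illustrated under assumptions.

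**Inputs from the article:** joint selection; at least one recording per professional per phase; two-sided testing at 0.05; a small number of professionals, with no figure given (Confidentiality).

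**Assumed inputs, not in the article:** normally distributed consultation scores; no true change in skill; 10 to 20 professionals; a visit-to-visit share of total variance *w* of 0.3 to 0.7; a correlation *ρ* of 0.5 to 1.0 between the selector's expectation and the score; a choice among *k* candidate visits.

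**Step 1: general form.** Let E(k) be the expected maximum of *k* standard normal values. In within-professional SD units, the spurious change is

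bias = ρ_post × E(k_post) − ρ_pre × E(k_pre).

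It is zero when selection is equally strong in both phases. With perfect foresight, best of 3 after and best of 2 before gives 0.846 − 0.564 = 0.282.

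**Step 2: upper bound.** Take an arbitrary visit before training, E(1) = 0, and perfect foresight after it, ρ = 1.
- Best of 2: E(2) = 1/√π = 0.564
- Best of 3: E(3) = 3/(2√π) = 0.846

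**Step 3: imperfect foresight.** With ρ = 0.5 the values halve: 0.5 × 0.564 = 0.28 and 0.5 × 0.846 = 0.42.

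**Step 4: total SD units and error rate.** Multiply by √w, with selection after training only.
- Best of 2: from 0.5 × √0.3 × 0.564 = 0.15 to 1.0 × √0.7 × 0.564 = 0.47
- Best of 3: from 0.5 × √0.3 × 0.846 = 0.23 to 1.0 × √0.7 × 0.846 = 0.71

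A simulation (4,000 runs per scenario, one recording per phase, paired t test at two-sided 0.05) gave:

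| Visit filmed after training | Spurious gain, total SD | False-positive rate |
|---|---|---|
| Unselected | about 0 | 4–6% |
| Best of 2 | 0.16–0.47 | 9–47% |
| Best of 3 | 0.23–0.72 | 15–83% |

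The unselected row is what consecutive or random sampling in both phases would give.

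**Step 5: what can still be changed.** BreeZe was introduced in June, September and November 2024 (Trial Design). Recordings before implementation should therefore exist, and the 3-month recordings fell due between September 2024 and February 2025. The 12-month recordings fell due between June and November 2025. The article postdates the close of recruitment on June 30, 2025, and analysis starts in August 2026 (Results).

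**The case against.** The strongest reply is that the article states one selection rule and does not vary it by phase. Being filmed and rated is a reason to prefer a cooperative patient before training as well as after it, and equal selection leaves the change unbiased. This stands. A reader might infer that the bias must run upward and cannot cancel; the document does not show that. It shows only that nothing in the stated rule keeps selection equal while the phase is known.

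Second, visits are picked days ahead and the research team shares the choice, so perfect foresight is unrealistic. This also stands, and it makes 0.56 and 0.85 upper bounds.

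Third, professionals are asked to use BreeZe in routine aftercare, so a filmed visit that contains the self-management web or goal setting is partly the intended effect. This is correct. Presence of BreeZe elements should not be treated as an artefact or adjusted away.

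Fourth, a reader might say that the videos inherit self-report bias. They do not: independent researchers code them. The weakness is in sampling, which is a separate matter.

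None of these replies supplies a sampling rule. The selection procedure is stated in the article, so this is more than a detail left to a fuller document.

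**Conclusion.** The point holds in conditional form. The stated procedure lets the pre-to-post change in COUNSEL-CCE and NCIT scores partly reflect which visits were filmed, if selection is stronger or of a different kind after training. With equal selection in both phases, the bias in the change is zero. With selection after training only and perfect foresight, it is at most about 0.56 (best of 2) or 0.85 (best of 3) within-professional SD, and about 0.28 or 0.42 at a correlation of 0.5. These figures rest on assumed normality and assumed candidate numbers; the article gives no data to narrow them.

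The consequence is limited. Table 1 lists need-supportive counseling as a secondary outcome at professional level, and the coprimary PiH analysis does not use the videos.

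**What to change.** As a design rule, use one procedure in every phase. The research team takes consecutive or randomly drawn eligible aftercare visits for each professional, without the professional's choice, and keeps a log of visits offered, declined and replaced.

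Where recordings already exist, do not switch the rule for the remaining time point alone, since that would itself make selection differ between phases. Instead:
- Document for each recording how it was selected and by whom.
- Classify each recording by stage of aftercare, for example time since discharge or first versus later visit. Do not classify by whether BreeZe was used, because that is part of the effect.
- Include stage as a covariate in the planned repeated-measures model.
- Qualify the claim of objective evaluation in the Outcomes section: coding is independent, but the visits were jointly selected.

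The covariate handles differences in stage only. It cannot remove the choice of an easier patient within a stage, which is why the claim also needs qualifying.

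The cost is less freedom in scheduling where the rule can still be applied, some retrospective documentation, and one extra covariate in a small sample. No additional recordings, equipment or coders are needed.
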